#### WP 2b—interviews with healthcare professionals

Interviews with healthcare professionals approximately 12 months after intervention implementation. We anticipate 30 one-off semi-structured interviews either face-to-face, phone or secure videoconferencing platform (e.g., MSTeams/Zoom). A bespoke topic guide (online supplemental file 2) informed by NPT^20 21^ will be used to explore healthcare professionals’ experiences of implementing the NHS TDS. Interviews will last no longer than 1 hour and will be audio-recorded or video-recorded and transcribed verbatim by a professional transcription company.

#### WP 2c—interviews with smokers

We anticipate approximately 50 one-off semi-structured interviews with smokers (based on the sampling criteria above) either face-to-face, phone or secure videoconferencing software (e.g., MS Teams/Zoom). A bespoke topic guide (online supplemental file 3) informed by TFA^22^ will be used to explore smokers’ experiences of the tobacco dependence service. Interviews will last approximately 1 hour and will be audio-recorded or video-recorded and transcribed verbatim by a professional transcription company. Data collection and recruitment will be guided by data saturation and information power, as aligned with the evaluation aims and proposed methods (including the application of theory and analytical method).^14 15^

#### Analysis: survey

Data will be managed using STATA.^23^ Questionnaires will be analysed descriptively, using absolute (n) and relative frequencies, means and SD as appropriate to the level of data, and 95% CI.^24^ Mean scores for each of the four NPT constructs and the six COM-B constructs will be calculated.^25^ Higher positive scores on NPT constructs are suggestive of greater potential for the NHS TDS to ‘normalise’ or become routinised.

#### Analysis: interviews

Interview data will be managed using NVivo^16^ and will be analysed using framework analysis^26^ by members of the research team. The framework method is systematic in allowing us to use coding frameworks informed by either NPT or TFA. While offering the flexibility of being able to derive themes inductively to capture implementation issues that might not fit ‘neatly’ into either NPT or TFA constructs.

### WP 3: effectiveness and process analysis (months 25–48)

#### Design

This quantitative non-randomised observational study aims to assess the reach of the service as well as the effect on health outcomes (effectiveness) and healthcare use (service uptake).

#### Population

All adults (aged 18 and over) who are identified as smokers in acute hospital, maternity or mental health settings, are offered the service in any of the participating NHS Trusts within the five evaluation regions and have recorded notes available to the research team between December 2022 and March 2025 will be included in this analysis of individual patient data. While no formal sample size calculation was conducted, we estimate approximately 69 000 potential individuals for inclusion in the evaluation. This estimate was based on 11 participating NHS Trusts, approximately 7 months of data collection (taking into consideration potential data governance and submission delays/gaps), and a national smoking prevalence of 12.1% in England.

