### Evaluation sites

This evaluation will take place in five regions across England: West (Bristol), North East and North Cumbria, West Midlands, Yorkshire and Humber and Greater Manchester. As of 2021, the average smoking prevalence among adults in England aged 18 and over is 13%.^8^ All regions in the evaluation have smoking rates higher than those of the national average: Bristol at 16%, the North East at 15%, West Midlands at 14%, Yorkshire and Humber at 14% and Manchester at 17%.^8^ As of 2022, the average smoking prevalence at the time of delivery in England was 8.8%. Four regions had higher smoking prevalence than the national average: North East at 12.5%, West Midlands at 11.4%, Yorkshire and Humber at 11.6% and Manchester at 9.2%. However, Bristol was slightly lower at 8.4%. Regarding mental health, as of 2022, smoking prevalence among adults with a long-term mental health condition in England was 25.2%.^8^ Four regions were higher than the national average: West Midlands at 25.5%, Manchester at 31.0%, Bristol at 30.4% and Yorkshire and Humber at 27.5%; however, North East of England was lower with 23.5%.^8^

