#### Data collection

Data will be collected across acute, maternity and mental health settings. These will include individual patient-level data drawn from medical records. The data will be used to determine:

Process outcomes: The service delivery and uptake (ie, the number of inpatients with smoking status recorded), the number of patients referred to the in-house service, number of those who were referred and were seen, the number of those who were referred who do receive treatment while in hospital, and the number of those who were referred to additional services on discharge.

Behaviour/health outcomes: Post-discharge smoking status (28-day smoking status, carbon monoxide-validated smoking status, smoke-free births). In acute inpatient and mental health inpatient will include either 28-day smoking status or self-reported quit. In maternity settings, quit data will include carbon monoxide-validated smoking status, smoking status at 36 weeks, smoke-free births, or self-reported quit.

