#### Analysis

Findings will be reported descriptively. Frequencies and percentages (with 95% CI) will be reported. Subgroup analysis will be conducted and involve age, ethnicity, gender, regions, smoking status at admission, referral to in-house tobacco treatment team, tobacco care plan, onwards referral made, 28-day smoking status and smoking status at the time of delivery and at 36 weeks. We will also stratify findings by Lower Super Output Areas and Index of Multiple Deprivation, to explore whether there are inequalities in service delivery/uptake.

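### WP 3 includes only identified smokers who were offered the service, so reach, smoking-status recording and inequality in screening or offer cannot be estimated from that population

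*Protocol article*

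**What the plan says.** Under WP 3, Population, the protocol article admits adults "who are identified as smokers in acute hospital, maternity or mental health settings" who also "are offered the service in any of the participating NHS Trusts within the five evaluation regions" and whose notes are available to the research team. It is these people who "will be included in this analysis of individual patient data". No other WP 3 population is defined.

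The neighbouring sections ask WP 3 for more than that group can show:

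- WP 3, Design: the study "aims to assess the reach of the service".
- WP 3, Data collection: the first process outcome is "the number of inpatients with smoking status recorded". Referral, being seen, treatment in hospital and onward referral follow.
- WP 3, Analysis: frequencies and percentages with 95% CIs, subgroups that include smoking status at admission, and stratification by small area and deprivation index "to explore whether there are inequalities in service delivery/uptake".

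Table 2 also assigns the level of participation in the service to WP 3. Table 3 puts better recording of smoking status first among the short-term outcomes, and the text below it names widening inequality as a possible unintended consequence.

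**The concern.** The pathway starts with asking about smoking, identifying the smoker and offering support. A service meant for everyone admitted can fail at any of these steps, or fail more often in some groups than in others. The inclusion rule keeps only patients for whom all of them succeeded. A result on reach, on recording or on equity of offer, drawn from that group, would be fixed by the selection and would carry no information about the trusts.

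At stake are one stated aim (reach), the first process outcome (recording) and the early part of the equity question. The Discussion section intends recommendations that guard against widening inequalities. Those would rest on data from which patients who were missed or passed over had been removed.

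**Working it through.** **1. The plan's own figure.** WP 3, Population, estimates about 69,000 potential individuals from 11 trusts, about 7 months of data and a prevalence of 12.1%. The implied form is

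N = trusts × months × patients per trust-month × prevalence.

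Patients per trust-month are not given, so the figure can be neither confirmed nor refuted. Solving backwards:

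- 69,000 / 0.121 = 570,248 patients in all
- 570,248 / (11 × 7) = 7,406 patients per trust-month

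The stated inputs contain no factor for being identified or being offered. As described, 69,000 counts expected smokers. It equals the WP 3 population only if every smoker is both identified and offered.

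**2. Does the population contain each outcome's denominator?** Write R for status recorded, O for offered, and "included" for meeting the WP 3 rule. Inclusion requires identification as a smoker, which implies R, and it requires O. Hence, in any stratum s,

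P(R | included, s) = 1 and P(O | included, s) = 1.

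| Quantity | Denominator needed | Held in WP 3 as defined? |
|---|---|---|
| Status recorded | All admissions or bookings | No. The proportion is 100%; the count lacks recorded non-smokers and smokers not offered |
| Reach | All smokers | No. 100% by construction |
| Inequality in screening or offer | All patients, or all identified smokers, by stratum | No. 100% in every stratum |
| Smoking status at admission as a subgroup | Smokers and non-smokers | No smoker/non-smoker contrast remains |
| Referral among those offered | Those offered | Yes |
| Seen, treated, referred onward | Those referred | Yes, for those offered |
| Quit outcomes | Those offered or referred | Yes |
| Inequality in any step after the offer | Those offered, by stratum | Yes |

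**3. How much could be hidden? (assumed rates; the article gives none)** Let r be the share of smokers identified and o the share of those offered. Then

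reach = r × o, and the WP 3 population = 69,000 × r × o.

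- r = 0.60, o = 0.30: reach 0.18, population 69,000 × 0.18 = 12,420
- r = 0.80, o = 0.60: reach 0.48, population 33,120
- r = 1.00, o = 1.00: reach 1.00, population 69,000

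In every row the offered share within the WP 3 population is 1.00.

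For equity, assume that 50% of identified smokers are offered in the most deprived stratum and 80% in the least deprived, with 40% uptake after offer in both, and take 10,000 identified smokers in each:

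- Most deprived: 5,000 offered, 2,000 take it up. Within WP 3, 2,000 / 5,000 = 40%. Over all identified smokers, 2,000 / 10,000 = 20%.
- Least deprived: 8,000 offered, 3,200 take it up. Within WP 3, 3,200 / 8,000 = 40%. Over all identified smokers, 3,200 / 10,000 = 32%.

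The 12-point difference does not appear in the analysis as defined.

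**The case against.** The strongest defence is that the inclusion rule governs patient-level data only. WP 3, Data collection, says that the data will include such records, so aggregate counts from the trusts are not ruled out, and a condensed article may leave their source to the full protocol. This stands in part: aggregates are possible. But the article names none, and it states a population that conflicts with its own aim and first outcome. That is a contradiction and not an omitted detail.

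A second defence is that support is meant for everyone admitted, so being offered may exclude few identified smokers. The size of that exclusion is indeed unknown. Whether the offer reached everyone is nevertheless what an evaluation of reach has to test, and the identification condition alone still fixes recording at 100% and leaves unidentified smokers out.

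Third, most of the pathway survives. Referral is itself a delivery step and stays computable among those offered, and participation among those offered is a fair reading of the Table 2 objective. This stands, and it limits the point to the steps up to the offer.

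A reader might infer two stronger things.

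- That the equity results are biased towards no difference in general. This holds only for screening and offer, where the contrast vanishes by definition. At later steps, selection on the offer can narrow, widen or reverse a gap, depending on who is offered.
- That 69,000 is too low. It uses "a national smoking prevalence of 12.1% in England", whereas Evaluation sites gives 13% nationally as of 2021 and states: "All regions in the evaluation have smoking rates higher than those of the national average". But 12.1% carries no year. The general-adult regional rates of 14% to 17% also do not describe a mix of acute, maternity and mental health patients, for whom the same section gives 8.4% to 12.5% at delivery and 23.5% to 31.0% with long-term mental illness. Without the setting mix, no rescaling is supported. Little turns on it anyway: at 69,000 the widest 95% half-width for a proportion is 1.96 × √(0.25 / 69,000) = 0.0037, or 0.37 points under simple random sampling.

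**Conclusion.** The point holds for everything up to and including the offer. In the population as defined, the recorded and offered proportions are 100% in every stratum, whatever the trusts did. Reach, status recording and inequality in screening or offer cannot be estimated from it. This follows from the inclusion rule and needs no assumed rate.

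The size of what is hidden is unknown. The ranges of 12,420 to 69,000 people and 18% to 100% reach, and the contrast of 20% against 32%, rest on assumed rates and show only what could go unseen. Outcomes after the offer, and inequalities in them, are unaffected so long as they are described as applying to smokers who were offered the service. The documents support no claim about the direction of bias at those later steps and no replacement for 69,000, only a clearer label for it.

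**What to change.** Set the population by outcome in WP 3:

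1. All adult admissions or antenatal bookings in the window, as aggregate counts by trust and setting, and by deprivation, ethnicity and age where trusts can supply them: for status recording.
2. All identified smokers, offered or not: for offer and referral.
3. Those offered or referred: for seen, treated and quit.

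Run the equity comparisons at each level that the data allow. Reach over all smokers then combines levels 1 and 2 and needs a stated assumption about smoking among patients with no recorded status.

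If the counts for level 1 cannot be obtained, withdraw the status-recording outcome and limit the reach and equity conclusions to identified smokers. If level 2 is also unavailable, limit them to smokers offered the service. Label 69,000 as expected smokers, both here and under WP 4, Population, where it is repeated. The same restriction does less harm in WP 4, which costs service users.

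The cost is revised population wording, an extract that keeps identified smokers who were not offered, and an added aggregate request to 11 trusts. Breakdowns may come back incomplete, and the article already allows for governance and submission delays, so the request should go out early.

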#### Data collection

Data will be collected across acute, maternity and mental health settings. These will include individual patient-level data drawn from medical records. The data will be used to determine:

Process outcomes: The service delivery and uptake (ie, the number of inpatients with smoking status recorded), the number of patients referred to the in-house service, number of those who were referred and were seen, the number of those who were referred who do receive treatment while in hospital, and the number of those who were referred to additional services on discharge.

Behaviour/health outcomes: Post-discharge smoking status (28-day smoking status, carbon monoxide-validated smoking status, smoke-free births). In acute inpatient and mental health inpatient will include either 28-day smoking status or self-reported quit. In maternity settings, quit data will include carbon monoxide-validated smoking status, smoking status at 36 weeks, smoke-free births, or self-reported quit.

#### Analysis

Findings will be reported descriptively. Frequencies and percentages (with 95% CI) will be reported. Subgroup analysis will be conducted and involve age, ethnicity, gender, regions, smoking status at admission, referral to in-house tobacco treatment team, tobacco care plan, onwards referral made, 28-day smoking status and smoking status at the time of delivery and at 36 weeks. We will also stratify findings by Lower Super Output Areas and Index of Multiple Deprivation, to explore whether there are inequalities in service delivery/uptake.

### WP 4: health economic analysis (months 25–48)

#### Design

This quantitative non-randomised observational WP aims to explore the cost of offering the service and if sufficient high-quality data are available to estimate the return on investment in the form of a cost per quit.

The economic evaluation will be undertaken from the perspective of the healthcare provider. A costing analysis will be conducted to explore the cost of providing the service once it has been implemented in a trust.

#### Population

Adults (aged 18 and over) who are identified as smokers in acute hospital, maternity or mental health settings and offered the service in any of the participating NHS Trusts within the five evaluation regions. While no formal sample size calculation was conducted, we estimate approximately 69 000 potential individuals for inclusion in the evaluation (based on 11 participating NHS Trusts, approximately 7 months of data collection, and a national smoking prevalence of 12.1% in England).

#### Data collection

Data on quit rates will be collected across acute, maternity and mental health settings. Quit data for acute inpatient and mental health inpatient will include either 28-day smoking status or self-reported quit. In maternity settings, quit data will include carbon monoxide-validated smoking status, smoking status at 36 weeks, smoke-free births or self-reported quit. All individual patient-level data will be drawn from medical records. Data on costs will be determined from findings from WP 1 and WP 2, discussions with the wider project team, appropriate information gathered from the different trusts, and previous studies in this area.^27^

#### Analysis

The health economic analysis will take a bottom-up approach to estimate the cost of providing the service per service user once it has been implemented in the trust. Where sufficient data are available, a cost per quit will be estimated.

A model of a service user’s pathway through the service will be developed based on the draft pathways provided in the protocol. Each component of the pathway will be costed in collaboration with service managers. The pathway will be altered as required to meet the trust-specific service pathway. The cost for the full pathway will be calculated per service user.

The primary analysis will be at a trust level; however, if sufficient data are available, a pathway-specific cost for the three different pathways (acute, maternity, mental health) will be calculated.

The perspective of the costs will be the healthcare provider and will be based on the standard approach used in economic evaluation, which involves identifying, measuring and valuing all appropriate costs.^28^ Several cost categories will be considered, including staff costs (eg, tobacco treatment advisors) and ongoing non-staff costs (such as consumables and training courses). Costs will be calculated in Great British pounds corresponding to prices in the ‘cost year’ of the evaluation (2021/2022). Where required, relevant unit costs will be gathered from routine data sources.^29 30^

Where sufficient data are available, the costs of the intervention will be combined with the quit rates calculated in WP 3 to estimate a return on investment (in the form of an estimated cost per quit). Return on investment can be thought of as representing the ‘rate of return’ from an investment.^31^ If sufficient data are available regarding the different pathways (acute, maternity, mental health) a separate estimated cost per quit will be calculated for each pathway.

### Integration and synthesis of all WPs

To triangulate and integrate the data from the four work packages, we will apply methods suggested by Farmer *et al*.^32^ Integration will involve identifying key themes or findings from each of the work packages and grouping these. Then, these findings will be compared against each other. Researchers involved in the analysis will also compare each other’s interpretation of the findings. The evaluation flowchart is presented in figure 1.

**Figure 1 F1:**
[figure not shown]
Evaluation flowchart (in work packages).

### Patient, public and stakeholder involvement

The views and experiences of the public and those most affected by smoking-related illness are an integral part of this project. To ensure this research is shaped by, and reflective of, these views, we will work with a project-specific Public Advisory Group (PAG) comprised of a small group of public advisors (n=4) from across England who are either past or present smokers and/or have relevant experience of NHS inpatient acute, mental health or maternity services. The PAG will be an integral part of our wider team contributing to a number of areas including, but not limited to, study materials development, wider public engagement and recruitment plans, study analysis and outcomes and dissemination. For example, the PAG have been involved in every stage of development of all work packages, as well as write-up of the protocol. A Public Involvement and Community Engagement Lead (AW) will be embedded within the core team to ensure the public voice is prioritised and incorporated into all stages of the project.

Importantly, this programme of work was prioritised for funding by the NIHR ARC Prevention Consortium’s Stakeholder and Public Advisory Groups. Draft versions of our funding application and protocol have been reviewed by members of the public, health and care commissioners, policy stakeholders and academic partners to determine the methodological robustness and acceptability of our plans and identify areas for improvement. Feedback from this prioritisation and review process has resulted in the revision of the protocol such as ensuring that we gathered evidence on how the service fits into the wider landscape at a local level (i.e., through qualitative work and ongoing relationships with regional and national implementation partners); revising the terminology throughout our work to highlight that tobacco smoking is a chronic, relapsing condition which is a leading cause of death and disability in the UK and therefore warrants appropriate treatment and support; and developing a health economics work package to determine costs and resource-use associated with delivering the service.

## Discussion

We anticipate this mixed-method evaluation of a nationally provided tobacco dependence service to generate evidence regarding its implementation, drawn from all settings (i.e., acute hospital, maternity and inpatient mental health), across five regions in England. Localised and context-dependent implementation strategies, both successful and unsuccessful, will form recommendations for future iterations of this national policy. Moreover, the evaluation will support national-level assessment of the impact of the service on health outcomes, through planned statistical and health economic analyses. Taken together, integrated data from the various work packages will allow us to identify variations in service provision, and make recommendations for enhancing implementation, tailored to local contexts, to mitigate the risk of widening health inequalities. Our ongoing and sustained relationships with lay, clinical, policy, academic and practice partners will also support the co-production of key findings from this work, which will be disseminated widely, to advance research, policy and practice relating to addressing tobacco dependence in England.

